### Data management

Study data will be collected and managed using REDCap (Research Electronic Data Capture) [52]. The study will be monitored early on during the study (after ten participants have been randomised), at study close-out and twice during the course of the trial.

### Statistical analysis

All statistical analyses will be performed using SAS version 9.4 (SAS Institute Inc. Cary NC), and R [53]. Analyses will be undertaken on an intention-to-treat basis. For the main analyses, all participants lost to follow-up will be presumed to be smoking. Per-protocol analysis will be undertaken for the primary outcome where participants with major protocol violations (e.g. cross-overs treatments, withdrawals, and loss to follow-up) will be excluded. Sensitivity analyses will be carried out to determine the effect of missing data and if the level of missing data is deemed high (i.e. > 20%) use of multiple imputation will be employed. Participant flow through the trial will be described in a Consolidated Standards of Reporting Trials (CONSORT) diagram. The number of withdrawals will be summarised by type, treatment group and time, with reasons where provided. Incidence rates, risk difference, RR and 95% CI will be calculated for all binary outcomes, and groups will be compared using chi-squared tests and multiple logistic regression analysis where appropriate. Continuous outcomes will be analysed using multiple linear regression modelling or non-parametric analysis. K6 and change in cigarettes smoked per day (in non-abstainers) will be analysed using repeated measures models, and will adjust for baseline value. Time to relapse will be analysed using Kaplan Meier curves, log-rank test, and Cox proportional hazards regression analysis. Secondary analyses will be conducted to determine the impact of varying cut-offs used for CO measurements, and secondary analyses performed with cessation rates corrected for discordance between reported and CO-verified cessation. The consistency of effects for pre-specified subgroups will be assessed using tests for heterogeneity. Subgroups will be based on sex, ethnicity, and type of cigarette.

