### Secondary outcome measures

The following secondary outcome measures will be assessed at randomisation, then at six, 12 and 24 weeks post-randomisation (Table 1):*Continuous abstinence (6 and 12 weeks)*: The proportion of participants that have stopped smoking defined as smoking not more than five cigarettes in total from randomisation (self-reported) (biochemically validated using a CO reading of ≤10 ppm at 24 weeks);*Seven-day point prevalence abstinence*: The proportion of participants that have stopped smoking, defined as self-report of smoking no cigarettes at all, not even a single puff in the last seven days;*Time to first lapse*: Defined as time to first cigarette smoked, even a single puff;*Time to first relapse*: Defined as time to smoking more than five cigarettes a day for three or more days in a row;*Change from randomisation in cigarettes smoked per day*: If the participant is still smoking;*Smoking reduction*: Defined as reducing consumption by ≥50% (in terms of numbers of cigarettes per day, weight of loose tobacco per day, or when smoking for non-daily smokers);*Change from randomisation in the physical signs and symptoms associated with withdrawal (randomisation and 6 weeks)***:** Measured using the Mood and Physical Symptoms Scale (MPSS) [47], including urge to smoke;*Concomitant medication*;*Use of any other smoking cessation methods*: NRT, non-NRT methods of cessation such clonidine, nortriptyline, acupuncture, Quitline, etc.;*Alcohol and drug use/severity of AOD problems (12 and 24 weeks only)*: Measured using the ASSIST-FC [45];*Mental health symptoms*: Measured using the K6 [46];*Health-related quality of life (randomisation and 24 weeks only):* Measured using the NZ EQ-5D Tariff 2 (telephone script) [50];*Confidence in ability to quit (randomisation only):* Measured on a Likert scale of 1 to 5, where 1 = ‘not very’ and 5 = ‘very’;*Adverse events*: Information regarding adverse events and whether they are related to treatment;*Medication compliance (randomisation, 6 and 12 weeks):* Self-reported frequency of using allocated product;*Crossover*: Participants in the varenicline only or varenicline + bupropion groups will be asked whether they accessed and used an EC (with or without nicotine) in the follow-up period;*Additional EC support (6 and 12 weeks):* Participants allocated to the varenicline + EC group will be asked whether they accessed any (on-line) EC support networks or bought different e-juice or EC during the trial;*Dual use (6 and 12 weeks):* Defined as use of both their allocated treatment and continued smoking of cigarettes;*Continuation of use (24 weeks):* Defined as continued use of their allocated treatment after the end of the designed 12 week treatment period;*Perception of the product (24 weeks only):* Participants will be asked for their views on use of their allocated treatment as a smoking cessation aid;*Acceptability/Recommendations* (*24 weeks only):* Participants will be asked whether they would recommend their allocated treatment to another smoker who wanted to quit.

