
### Sample size

A sample size of 338 (169 in each arm) anticipates a 30% loss-to-follow-up and will confer 80% power, 2-sided *p* = 0.05 to detect an absolute difference of 15% between the varenicline plus EC group and varenicline alone group in 24 week carbon monoxide (≤10 ppm) verified abstinence rates, with a predicted abstinence rate in the varenicline plus EC group of 30%. The anticipated 30% loss-to-follow-up is more than the 22% noted in the psychiatric cohort in the EAGLES trial [14] but lower than the 39% found in the Ebbert et al. trial [38]. We estimate 30% of participants will collect and use the prescribed varenicline for the first 2 weeks of the study [51], and that most (around 80%) of this group will be varenicline non-responders after 2 weeks of medication use [23]. Thus, 507 people will need to be recruited into the ‘initial treatment phase’ in order to obtain 338 people to be randomised. We anticipate it will take 16 months to recruit 338 participants.

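### Change in cigarettes per day is compared between arms only among non-abstainers, so this secondary result is not a randomised comparison and its bias has no determinable sign

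*Protocol article*

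**What the plan says.** Three parts of the protocol article bear on this.

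- **Secondary outcome measures** defines change from randomisation in cigarettes smoked per day with the condition "If the participant is still smoking". The same list has a separate binary smoking-reduction outcome, "Defined as reducing consumption by ≥50"%, whose text does not restrict it to continuing smokers.
- **Statistical analysis** says: "K6 and change in cigarettes smoked per day (in non-abstainers) will be analysed using repeated measures models, and will adjust for baseline value". It also says "Analyses will be undertaken on an intention-to-treat basis" and, for the main analyses, that "all participants lost to follow-up will be presumed to be smoking".
- **Sample size** plans for "80% power, 2-sided *p* = 0.05 to detect an absolute difference of 15"%, "with a predicted abstinence rate in the varenicline plus EC group of 30"%. The implied rate on varenicline alone is therefore 30 - 15 = 15%.

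**The concern.** Whether a participant is a non-abstainer is known only after randomisation, and changing that status is what the EC is meant to do. If the trial succeeds, the two sets of remaining smokers have been filtered differently. Their difference then mixes any effect of the EC on consumption with a difference in who is left. Randomisation no longer protects the comparison, although the section declares an intention-to-treat basis.

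There is also a loss of information. People who went from their usual consumption to zero have reduced the most, and the model excludes them. If the EC worked only by making people quit, the planned analysis could show no difference in consumption while average consumption in the randomised arms differed clearly.

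What is at stake is the reading of one secondary result. It could be reported as an effect, or as no effect, of the EC on how much people smoke when it is neither.

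**Working it through.** **1. Design rates.** The sample size confirms that 30% and 15% are the rates planned for. With an unpooled normal approximation, n per arm = (1.96 + 0.842)² × (0.15 × 0.85 + 0.30 × 0.70) / 0.15² = 7.849 × 0.3375 / 0.0225 = 117.7, rounded up to 118. Allowing for 30% loss, 118 / 0.70 = 168.6, so 169 per arm and 338 in total. The stated figure is reproduced.

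**2. Who would be compared.** At 24 weeks the non-abstainers number 169 × 0.85 = 144 on varenicline alone and 169 × 0.70 = 118 on varenicline plus EC. Among about 118 per arm followed up, they are about 118 × 0.85 = 100 and 118 × 0.70 = 83. The rates are for verified continuous abstinence at 24 weeks; the sets at 6 and 12 weeks can differ.

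**3. What is left out.** Let *m* be mean cigarettes per day among continuing smokers, equal in both arms. The mean over everyone randomised is (1 - quit rate) × *m*, so the arm difference is (0.70 - 0.85) × *m* = -0.15*m*. The article gives no *m*. For an assumed *m* of 10 to 20 the difference is -1.5 to -3.0 cigarettes per day. In this case the non-abstainer analysis shows zero.

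**4. Direction and size of the selection bias.** This was simulated with 2,000,000 participants and a single follow-up visit. All of the following inputs are assumptions:

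- Starting consumption B has mean 20 and SD 8.
- Latent dependence U is independent of B.
- Consumption if still smoking is 0.8B + 4U + error, with error SD 4.
- Quit rates are fixed at 15% and 30%.
- The EC has no effect on consumption in continuing smokers.

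The non-abstainer model regresses change on arm and B. A positive difference means the EC arm looks worse.

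| Who quits | Non-abstainers, adjusted | All randomised, abstainers = 0 |
|---|---|---|
| Unrelated to dependence | -0.01 | -2.44 |
| Depends on B only (moderate; strong) | 0.00; 0.00 | -2.02; -1.82 |
| Depends on U only (moderate; strong) | +0.27; +0.48 | -2.28; -2.18 |
| Depends on B and U (moderate; strong) | +0.28; +0.44 | -2.04; -1.85 |
| EC mainly makes lighter-dependent smokers quit (moderate; strong) | +0.62; +0.79 | -1.46; -1.34 |
| EC mainly helps heavier smokers | -0.85 | -3.98 |

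If the EC truly lowers consumption by 1 per day in continuing smokers, the non-abstainer estimate is -0.71 when quitting depends moderately on B and U. It is -0.21 in the strongest scenario against the EC.

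A separate simulation assumed a correlation of 0.3 to 0.7 between propensity to quit and to cut down, with a mean of about 16.6 per day at randomisation. It gave +0.4 to +0.9. It did not vary whom the EC helps, so it could show only one sign.

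**5. Bias against noise.** The residual SD in the first simulation is √(4² + 4²) = 5.7. With 100 and 83 smokers, SE = 5.7 × √(1/100 + 1/83) = 0.85. The bias in the table is at most about one standard error.

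**The case against.** The strongest reply is that the article is open about the condition. It asks whether those who did not quit cut down, which is a legitimate clinical question. Entering abstainers as 0 answers a different one: with no effect in continuing smokers, the all-randomised difference only restates the abstinence effect in cigarettes per day, and abstinence is already the primary outcome. The model also adjusts for baseline, which removes selection acting through baseline consumption.

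Much of this stands. The non-abstainer result is worth reporting, and the all-randomised estimate does partly reflect quitting. But stating a condition openly does not restore randomisation, and one consumption value removes only the selection that passes through it. The article measures cigarette dependence separately, yet names only the baseline value for this model.

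A reader might infer more than the article supports:

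- **The EC will look harmful, or the sign will be wrong.** Nothing in the article says who would quit. The bias is zero if quitting acts only through baseline consumption and reverses if the EC mainly helps heavier smokers. In the scenarios run, a true reduction of 1 per day stayed favourable.
- **A repeated-measures model cannot cope with a changing set.** Such models fit participants with differing visits. The difficulty lies in what is being estimated.
- **The reduction message and the cost per person reducing depend on this model.** The binary 50% reduction outcome carries no such restriction. Nothing in the Cost-effectiveness section says the mean difference is used.
- **Adjusting for baseline when change is from randomisation is an error.** Baseline may simply mean the starting value, and fixing the covariate is normal analysis-plan detail. If the value before varenicline were meant, the consequence is lost precision, not bias. With unit variances (B = pre-varenicline, R = randomisation, Y = follow-up), the residual variance is 2(1 - r_RY) - (r_BR - r_BY)² instead of 1 - r_RY². Under assumed correlations of 0.5 to 0.8 that is 0.542/0.51 to 0.91/0.75, or 6% to 21% more.

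**Conclusion.** The concern holds in limited form. As written, the between-arm model for cigarettes per day compares groups formed by a post-randomisation status that is expected to differ by 15 percentage points. Its result is not a randomised or intention-to-treat treatment effect, and it omits reductions to zero.

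That conclusion rests on the article's own definitions and design rates. The sizes do not: the article gives no mean or SD of consumption and no relation between dependence and quitting. Under the assumptions shown, the bias runs from about -0.9 to +0.8 cigarettes per day and may be nil. Neither its amount nor its sign can be determined from the article.

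Severity is minor. This is one secondary outcome, and neither the primary outcome nor the binary reduction outcome is affected.

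**What to change.** Make the between-arm analysis of cigarettes per day one in all randomised participants, with abstainers entered as 0. Use a method suited to the spike at 0, such as a repeated-measures count model or a rank-based comparison. Adjust for the value at randomisation, since change is defined from there. Participants lost to follow-up are presumed smoking but have no count, so the analysis plan should say how they enter this model.

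Keep the non-abstainer analysis as supplementary, labelled as conditional on continued smoking and not a randomised treatment effect. Report the two side by side, because the all-randomised estimate partly reflects the abstinence effect and a reader needs both to see where a difference comes from.

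The cost is one paragraph of analysis wording. Consumption is already collected at randomisation and at 6, 12 and 24 weeks, so no new data are needed.

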### Cost-effectiveness

Cost outcomes will include cost per quitter, cost per person reducing their daily cigarette consumption, and incremental cost effectiveness ratio should the intervention prove to be effective. Comparative cost-utility will be estimated using the NZ EQ-5D tariff 2 [50]. We will compare our data with data from NZ cessation service providers and international studies. This modelling will take a health sector perspective. To give a societal perspective on the benefits (especially to low-income smokers) tobacco expenditure savings to individual smokers who quit and cut down will also be calculated using data on the daily amount smoked prior to quitting and the price of the particular products smoked. A range of approaches to assessing the benefit of years per life saved will also be explored.

### Ethical considerations

Ethics approval for the trial was obtained on 26/09/2016 from the Southern Health and Disability Ethics Committees (16/STH/153). Two subsequent amendments to the study protocol were approved on 4/09/2017 and 8/12/2017. Approval from the NZ Standing Committee on Therapeutic Trials (SCOTT) was obtained on 25/10/2016 for the use of ECs with nicotine (16/SCOTT/86).

### Trial governance

Trial governance includes a steering committee (on which all authors sit), and a trial management team who will manage the day-to-day processes of the trial, including data management. A Data Safety Monitoring Committee (DMC) will be established for the trial. Members will have no conflicts of interest. The DMC will draw up their own terms of reference, will have clearly defined stopping rules in the event of safety concerns agreed upon by the Committee, and will be guided by statistical monitoring guidelines consistent with GCP. The study statistician will provide the DMC with reports on safety data.

### Dissemination policy

Results will be disseminated regardless of the magnitude or direction of treatment effect. Dissemination will include trial registration, feedback to trial participants, publication in an international journal, national and international media releases at the time of journal publication, and presentations to relevant local, national and international audiences (including health service funders and providers). In NZ this will include but is not limited to the Ministry of Health, District Health Boards (including CADS and CMHS), Primary Health Organisations, NGOs, health professionals, and Māori and Pacific organisations managing patients with mental illness and/or AOD addictions and/or involved in provision of smoking cessation support. Criteria for authorship of any papers rising from the trial will be taken from the International Committee of Medical Journal Editors.

## Discussion

The STATUS trial will be unique in that it is one of the first trials to evaluate a highly practicable, adaptive treatment approach to smoking cessation among smokers with mental illnesses and/or AOD addictions. Current evidence suggests that combining varenicline with NRT (including ECs with nicotine) increases quit rates over varenicline alone, whilst the efficacy of nicotine ECs may be enhanced when used in addition to varenicline. However, these approaches to treatment have not been integrated or trialed among people with mental illnesses and/or AOD addictions who are varenicline non-responders. The findings will be of wide interest given the universal difficulty in helping smokers with such problems to quit. Such people are often excluded from smoking cessation trials with an efficacy goal. If positive, our findings will provide healthcare providers with a simple yet effective tool to increase smokers’ chances of successful cessation via adapting treatment based on self-reported initial response. In addition, if positive, this approach could lead to significant cost savings via reducing medication waste in non-responders (who would otherwise continue with an ineffective treatment). The trial is currently ongoing; recruitment started on 31/05/2017, with recruitment expected to take 18 months. Trial findings are likely to be available July 2019.

## Abbreviations

AE: Adverse event
AOD: Alcohol and other drugs
ASSIST-FC: Alcohol, Smoking and Substance Involvement Screening Test Short Form
CADS: Community alcohol and drug services
CI: Confidence interval
CMHS: Community mental health services
CO: Carbon monoxide
COPD: Chronic obstructive pulmonary disease
EC: E-cigarette
FTCD: Fagerstrom Test for cigarette dependence
ITT: Intention-to-treat
K6: Kessler Psychological Distress Scale
mCEQ: Modified Cigarette Evaluation Questionnaire
MPSS: Mood and Physical Symptoms Scale
NGO: Non-governmental organisation
NRT: Nicotine replacement therapy
NZ: New Zealand
OR: Odds ratio
RCT: Randomised controlled trial
REDCap: Research Electronic Data Capture
RR: Relative risk
RYO: Roll your own
SCOTT: Standing committee on therapeutic trials
STATUS: Study of adaptive treatment for users of mental health and addiction services
